### Consent, data collection and follow-up

In the context of comatose patients resuscitated after cardiac arrest, it will not be possible to obtain prior informed consent from the patient himself. An emergency inclusion procedure will then be made possible. The detailed process of the inclusion process is provided in Supplemental Table 1.

### Study intervention and target temperature management

Overall study design is illustrated by Fig. 1. After admission to the ICU and putative etiological treatment, if required, eligible patients could be included for URTH induction by Vent2Cool. Patients will be sedated and paralyzed with atracuronium and monitoring of muscle paralysis is recommended whenever possible. The maintenance of sedation and muscle paralysis after the Ven2Cool procedure will be left to the discretion of the physicians. Surface cooling device, that will be necessary to maintain hypothermia after induction by Ven2Cool, will be pre-positioned in order to avoid mobilization immediately after this procedure. However, the surface cooling system will not be active at this stage and until the end of the Vent2Cool procedure.

**Fig. 1 f0005:**
[figure not shown]
Schematic representation of the study design. *ROSC, resumption of spontaneous circulation; TTM, target temperature management; mRS, modified Rankin Score.*

Once the inclusion process has been completed, the Vent2Cool system will be set up according to instruction for use, after installation of a single-use Breathing Circuit as well as a single-use bag containing sterile breathable liquid called “Liquid2Breathe”. Schematic illustrations and picture of the Vent2Cool system are illustrated in Fig. 2, Fig. 3, respectively. Prior to the beginning of the Vent2Cool procedure, the user will enter the Ideal Body Weight of the patient and confirm the pre-set parameters for end-expiratory liquid volume (EELqV), liquid tidal volume (Vt) and Fraction of oxygen in the gas mixture (FgO_2_). This is performed on the Vent2Cool touch screen in order to personalize the treatment (i.e. quantity of breathable liquid) for the given patient. The user will start the Vent2Cool procedure after disconnection of the endotracheal tube from the gas ventilator followed by a rapid secured connection to the Vent2Cool connector. Upon switching the Vent2Cool valve ON, the Vent2Cool system automatically fills the lungs with breathable liquid and starts URTH induction. Throughout the procedure, the user can modify EELqV (10–20 mg/kg IBW), Vt (6–9 ml/kg IBW) and the FgO_2_ (50–100%). Of note, FgO_2_ is fully distinct from the inhaled fraction of oxygen used in conventional ventilation as this is the fraction of oxygen in the gas mixture delivered by Vent2Cool into the breathable liquid, but not the fraction of in in the breathable liquid. The end of the procedure is expected to occur after reaching a core temperature of 33.0 °C and a procedure duration of less than 60 min. The investigator can stop the procedure at any moment for any safety reason. When stopping the procedure, the Vent2Cool system automatically withdraws the maximal amount of breathable liquids from the lung through a lung draining procedure. The user will end the Vent2Cool procedure by closing the patient connector valve a reconnecting the endotracheal tube to the gas ventilator. If required, the investigator will use bronchoscopy to suction residual amounts of breathable liquids. It will be suggested to maintain a Vt less than or equal to 6 ml/kg and a positive end-expiratory pressure (PEEP) of at least 5 cmH_2_0 for a minimum of 8 h following the procedure. The use of a heat and moisture exchanger (HME) on the respiratory circuit will be discouraged during this same period and the use of a heated humidifier should be favored.

**Fig. 2 f0010:**
[figure not shown]
Schematic illustration of the Vent2Cool system (left panel) and its graphic-user interface (right panel) delivering total liquid ventilation and ultra-rapid hypothermia.

**Fig. 3 f0015:**
[figure not shown]
Picture of the Vent2Cool system in the Intensive Care Unit.

After resumption of conventional ventilation, the body temperature of the patients will be maintained at 33.0 ± 0.5 °C by surface cooling devices for 24 h. As described above, the “pads” set up initially will be connected to the external thermal control device. After 24 h of hypothermia, patients will be rewarmed according to current protocols in the investigator's site. A rewarming rate of 0.25 to 0.5 °C/h will be recommended.

### Patients’ follow-up

After rewarming, patients will be followed according to the hospital practices. They could be weaned from the ventilator and extubated, according to the centers procedure with, e.g., PaO_2_ (arterial oxygen tension) / FiO_2_ (Inhaled oxygen) ratio > 200 mmHg, FiO_2_ < 50%, PEEP < 8 cmH_2_O, lack of vasopressor administration, cough reflex and respiratory rate / tidal ratio < 105. The previously mentioned secondary end-points will be monitored until Day 3 after cardiac arrest, as shown in Table 1, Table 2. We will collect the final cause of the initial of cardiac arrest, coronarography data (if available), results of other etiological examinations (e.g., brain CT-scan, chest CT-scan), electroencephalogram, time of rewarming and time of normothermia achievement.

Study will end by a last visit by the investigator 28 days after cardiac arrest (“face to face”). During this visit, the investigator will record the number of days under mechanical ventilation, the occurrence or not of weaning from mechanical ventilation, the number of days in intensive care unit (before transfer to another ward), the number of days before hospital discharge, the number of days alive and permanently out of hospital, in case of death, cause of death, the current treatments and dosages, body core temperature any delayed adverse effects that can be attributable to Vent2Cool. A chest-CT scan will be performed to evaluate the presence or nor pleural collection of PFOB.

### Study schedule

The enrolment phase in expected to last 11 months. Since study duration is 28 days for each patient, the overall study is expected to last 12 months.

### Sample size and statistical analysis

The analyses will be conducted on the following patient sets: Safety population (SAF), Full Analysis Set (FAS) and Population Per Protocol (PP). The SAF includes all included and patients treated by Vent2Cool. The FAS (according to the Intent-to-Treat (ITT) principle) includes all treated patients, who had one post-baseline evaluation. The PP population includes all patients of the FAS except those with any major protocol deviation, that might significantly affect the completeness, accuracy, and/or reliability of the study data. The main endpoint analysis and secondary endpoint analyses will be based on the Full Analysis Set. A supportive analysis will be based on the Per Protocol population if more than 10% of patients are excluded from FAS.

A summary table and a flow chart will be presented for each patient population presenting the number of patients at each assessment and identifying the number of patients who withdrew over time, with the reason of premature study termination. Patients may withdraw from the study at any time, with or without reason and without prejudice to further treatment. Data that have already been collected on prematurely withdrawn patients will be retained and used for analysis, but no new data will be collected after withdrawal. Patients lost to follow-up, after hospital discharge before the end of the study, will be replaced. Data collected until the last available visit of these patients will be analyzed.

Based on an estimated success rate of around 80%, a sample of 24 analyzable patients was calculated as required to achieve sufficient precision of the success rate using Wilson's score interval, with a 95% confidence interval. Specifically, 19 of the 24 patients will have to undergo the procedure successfully, giving an expected success rate of 79.2% (95% CI [59.5%; 90.8%]).

Quantitative parameters will be described using the following summary descriptive statistics: number of patients, mean, standard deviation, median, first and third quartiles, and minimum and maximum values. Mean and standard deviation values will be reported to one decimal place greater than the data were collected. Median, first and third quartiles, minimum and maximum values will be reported with the same precision, as they were collected. Qualitative parameters will be described using frequencies and percentages.

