### Trial objectives

The primary objective is to demonstrate the ability of the Vent2Cool medical system (Orixha, Paris, France) to perform hypothermic TLV. Vent2Cool performance and efficacy have been rigorously validated *in vitro* and *in vivo*.^11^, ^12^, ^13^, ^14^, ^15^, ^16^ URTH targeted the achievement of core body temperature of 33.0 ± 0.5 °C within 60 min after the start of the procedure in patients resuscitated after intra- or extra-hospital cardiac arrest.

As secondary objectives, the study will aim at demonstrating: the safety of the procedure, the cooling performance, the ability to be implemented in the emergency setting of post-cardiac arrest management, clinical outcomes and impact on biological markers.

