### Primary and secondary endpoints

The primary endpoint is the success of the procedure, defined as the ability to reach a body core temperature (bladder recommended) of 33.0 ± 0.5 °C and a safe return to conventional mechanical ventilation within less than one hour after Vent2Cool start. Start of the Vent2Cool procedure is defined as the opening of the Vent2Cool patient connector valve. Secondary endpoints are shown in Table 1, Table 2.

**Table 1 t0005:** Summary of the secondary safety endpoints.

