### Eligibility criteria

Eligible patients will be unconscious patients resuscitated after extra- or intra-hospital cardiac arrest and admitted to the Intensive Care Units (ICU). Cardiac arrest from presumed cardiac or asphyxial origin, regardless of the heart rate initially recorded, will be included. Patients must be aged between 18 and 84 years with an ideal body weight (IBW) comprised between 40 and 93 kgs. Inclusion and exclusion criteria are shown in Table 3.

**Table 3 t0015:** Summary of inclusion and exclusion criteria.

Inclusion criteria	Exclusion criteria
• Patient resuscitated after extra- or intra-hospital cardiac arrest, from presumed cardiac or asphyxial origin, regardless of the heart rate initially recorded.	• Conscious patient
• Age between 18 and 84 years old	• Patient Ideal Body Weight less than 40 kgs or more than 93 kgs
• Time between collapse and return of spontaneous circulation (ROSC) < 60 min	• Traumatic cardiac arrest, drowning, exsanguination or sepsis
• Presumption, at the time of inclusion, of a possibility of starting Vent2Cool within a period of less than 120 min after ROSC.	• Temperature at admission < 34.0 °C
• Unconscious (GCS < 8, not able to obey verbal commands after sustained ROSC)	• Need for veno-arterial extracorporeal circulation before ROSC
• Patient affiliated with a social security system (If applicable)	• One of the following signs at echocardiography at hospital admission: - Acute core pulmonale, defined by right ventricular enlargement with interventricular septal deviation, associated with a Tricuspid Annular Plane Systolic Excursion (TAPSE) < 12 mm and need for vasopressor agents - Time-velocity integral of subaortic flow < 10 m/s
• Consent of the member of patients’ family or that of the trusted person if present and able to understand; otherwise certificate of emergency inclusion in compliance with applicable regulations.	
• Vent2Cool must be connected to a standard cuffed ETT of 7.0 mm to 9.0 mm internal diameter for the procedure. For 7.0 mm ETT, the IBW setting should not exceed 75 kg. For ETTs of 7.5 to 9.0 mm, the full range of the IBW setting (i.e. 40 to 93 kg) can be applied.	
	• Wrong positioning or damage of the endotracheal tube.
	• Women under 50 years old (childbearing age) or for women of > 50 years old, a positive pregnancy test (urinary) in case of pregnancy suspicion by the investigator. Possible breastfeeding during the study.
	• Suspicion of intracranial bleeding

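### The primary analysis set is labelled intent-to-treat but is a treated-and-evaluated set, and no analysis set counts included patients in whom the device is never started

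*Protocol article*

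**What the plan says.** Three sets are defined in the Protocol article under Sample size and statistical analysis.

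- Safety set: "The SAF includes all included and patients treated by Vent2Cool".
- Full Analysis Set (FAS): "The FAS (according to the Intent-to-Treat (ITT) principle) includes all treated patients, who had one post-baseline evaluation".
- Per-protocol set (PP): the FAS minus patients with major deviations.

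On their use, the same section states: "The main endpoint analysis and secondary endpoint analyses will be based on the Full Analysis Set". The one supportive analysis is conditional: "A supportive analysis will be based on the Per Protocol population if more than 10% of patients are excluded from FAS".

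Under Primary and secondary endpoints, success means reaching the target core temperature and "a safe return to conventional mechanical ventilation within less than one hour after Vent2Cool start". The clock is fixed there too: "Start of the Vent2Cool procedure is defined as the opening of the Vent2Cool patient connector valve".

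Inclusion comes earlier. Table 3 requires a "Presumption, at the time of inclusion, of a possibility of starting Vent2Cool within a period of less than 120 min after ROSC", and Study intervention and target temperature management places device set-up after inclusion is complete. The Abstract names feasibility as an aim, and Trial objectives adds "the ability to be implemented in the emergency setting of post-cardiac arrest management".

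**The concern.** An intent-to-treat label tells the reader that nobody leaves the denominator because of what happened after entry. This set imposes two conditions that are met or failed only after entry: being treated, and having a post-baseline evaluation. They raise different issues.

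1. **Treated but not evaluated.** Such a patient has no documented success and would most plausibly be an immediate abort or collapse. A rule that can remove only likely failures can bias the primary rate in one direction only, and no reason is given for it.
2. **Included but never started.** These patients say nothing about how well a started procedure works. They do bear directly on whether the technique can be delivered in an emergency, which is a stated aim. No set retains them.

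**Working it through.** **Step 1. Who is in which set.**

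| Patient | Safety set | FAS | PP |
|---|---|---|---|
| Included, valve never opened | no | no | no |
| Valve opened, no post-baseline evaluation | yes | no | no |
| Valve opened, evaluated, major deviation | yes | yes | no |
| Valve opened, evaluated, no major deviation | yes | yes | yes |

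The supportive set (PP) is narrower than the primary set. Nothing widens the denominator.

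**Step 2. Can the first row occur?** Yes. Inclusion rests on a presumption of a timely start. Set-up, disconnection from the gas ventilator, connection to the device and valve opening all follow it.

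**Step 3. Can the second row occur?** Rarely. Table 2 schedules core temperature every minute from the start, Table 1 records early termination as an endpoint, and vital status is collected at Day 28. Almost any started patient should have some evaluation.

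**Step 4. Do the implementation endpoints fill the gap?** No. The two in Table 2 are the times to device start from ROSC and from ICU admission. Both exist only for started patients. The share started within 120 min can be derived among started patients, but no listed endpoint gives it among included patients.

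**Step 5. The plan's own figure.** The inputs are 19 successes, 24 analyzable patients and a 95% Wilson score interval (Sample size and statistical analysis). With p = x/n and z = 1.96:

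- centre = (p + z²/2n) / (1 + z²/n)
- half-width = z·√(p(1−p)/n + z²/4n²) / (1 + z²/n)

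For 19/24, p = 0.7917 and z²/n = 0.1601.

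- Centre = (0.7917 + 0.0800)/1.1601 = 0.7514
- Half-width = 1.96 × √(0.006872 + 0.001667)/1.1601 = 0.1561
- Interval: 59.5% to 90.8%, which matches the stated interval.

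**Step 6. Effect of the denominator.** The number excluded is not in the article, so the counts below are assumptions and zero is possible. The two groups are kept apart because they belong to different denominators.

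| Quantity | Patients added as not successful | Rate | 95% Wilson interval |
|---|---|---|---|
| Plan's figure | 0 | 19/24 = 79.2% | 59.5 to 90.8 |
| Primary set (valve opened) | 1 treated, not evaluated | 19/25 = 76.0% | 56.6 to 88.5 |
| Supportive, all included | 2 non-starts | 19/26 = 73.1% | 53.9 to 86.3 |
| Supportive, all included | 4 non-starts | 19/28 = 67.9% | 49.3 to 82.1 |

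Near 19/24, one added failure costs 79.2 − 76.0 = 3.2 percentage points.

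**Step 7. The PP trigger.** PP is formed by removing patients from the FAS. Read literally, the trigger counts patients who never entered the FAS. The likely intention is FAS patients left out of PP: 10% of 24 is 2.4, so 3 or more patients.

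**The case against.** The strongest reply is that a treated-patient denominator suits this endpoint. The trial has one arm, so there is no randomisation for intent-to-treat to protect. The endpoint is procedure success, timed from valve opening, and a patient whose valve was never opened has no time zero. This stands. It is why the primary set proposed below also leaves non-starts out.

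A reader might infer that the success rate is inflated, or that failed connections and non-starts are primary-endpoint failures wrongly dropped. The article supports neither reading. It gives no count of excluded patients, and if none are excluded the bias is zero. Connection to the device comes before the valve is switched on, so a failed connection is normally a pre-start event.

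It can also be said that the evaluation condition will exclude almost nobody, given the density of recording, and that the planned flow chart will show patient numbers. Both are fair. Rarity limits the harm but does not justify the rule, and a flow chart does not change the primary denominator. Finally, listings and missing-data rules may sit in the full protocol or analysis plan. The point here concerns what the article does state: the label, the two conditions and the three sets.

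**Conclusion.** The point holds in a limited form. The label contradicts the definition. The evaluation condition is unjustified and, if it ever operates, would most likely remove an immediate failure. Upward bias in the primary rate is therefore possible but not shown: about 3 percentage points for one such patient, and probably none in practice.

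The gap for the feasibility and implementation aims matters more. It does not depend on rarity, because the sets as defined cannot show how often an included patient failed to reach the start of the procedure. Its size depends wholly on the number of non-starts, which is unknown. The illustrative 2 and 4 assume that 24 patients enter the FAS, that 19 succeed, and that every non-start counts as not achieved.

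The PP trigger is a minor wording fault that does not affect the primary rate.

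**What to change.** - Remove the intent-to-treat label from the FAS.
- Define the primary set as every patient in whom the connector valve was opened, which is the start the article already defines. Count any missing or unassessable component of the endpoint as failure.
- Add a supportive success rate over all included patients, with non-starts counted as not achieved.
- Report the number included but not started, and the proportion of included patients started within 120 min of ROSC.
- Reword the PP trigger to *more than 10% of FAS patients excluded from PP*.

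The cost is a change of wording and slightly more analysis, using data already collected. No extra patients or assessments are needed. The reported rate may be a little lower.

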**Secondary safety endpoints**
• SaO_2_, PaO_2_ and PaCO_2_ at inclusion, 10 and 25 min after the start of Vent2Cool procedure and 1 h, 2 h, 12 h, 24 h, 48 h and 72 h after the end of procedure
• Occurrence of an episode of severe oxygen desaturation (SpO_2_ < 75%) on pulse oximeter lasting at least 5′ during the Vent2Cool procedure
• Occurrence of severe hypercapnia (PaCO_2_ > 75 mmHg); hyperoxemia (PaO_2_ > 400 mmHg); hypoxemia with PaO_2_ < 75 mmHg in arterial blood at t = 10 and 25 min after starting Vent2Cool procedure
• Occurrence of an episode of major systemic hypotension (invasive or non-invasive measurement) with systolic blood pressure < 60 mmHg during Vent2Cool procedure
• Heart rate measured from the EKG or blood pressure signal at 10 and 25 min after starting Vent2Cool procedure and at t = 1 h, 2 h, 12 h, 24 h, 48 h and 72 h after the procedure
• Systemic systolic and diastolic blood pressure at 10 and 25 min after starting Vent2Cool procedure and at t = 1 h, 2 h, 12 h, 24 h, 48 h and 72 h after the procedure
• Presence of arrhythmia or unexpected electrocardiographic abnormality
• Early termination of the Vent2Cool procedure before reaching a core target temperature below 33 ± 0.5 °C (failure of cooling induction)
• Number and percentage of patients for whom the core temperature has reached a value lower than 30 or 32 °C within 60 min after the start of the Vent2Cool procedure
• Adverse events related to Vent2Cool procedure, i.e., appearance of a perfluorothorax, unexpected cardiac arrhythmia or major hemodynamic instability, major hypoxemia during or immediately after the Vent2Cool procedure (i.e., during the first hour following the end of the procedure)
• Ventilatory parameters after the Vent2Cool procedure, i.e., measured values of positive end-expiratory pressure (PEEP), end-inspiratory pause pressure (Plateau pressure), driving pressure and static pulmonary compliance at t = 1 h, 2 h, 12 h, 24 h, 48 h and 72 h after the Vent2Cool procedure
• Occurrence of pulmonary infection in the ICU
• Presence or absence of pleural collection of perfluorocarbon in the lungs on thoracic computed tomography examination in patients surviving on Day 28 after cardiac arrest.

**Table 2 t0010:** Summary of the secondary endpoints for cooling performance, implementation in the care pathway, survival and neurological outcome, and clinical pathology.

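### As written, the Table 1 safety endpoints are analysed on the Full Analysis Set and the defined Safety population has no endpoint; the expected effect is small, and one sentence corrects it.

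*Protocol article*

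**What the plan says.** The section on sample size and statistical analysis in the protocol article names three analysis sets: Safety (SAF), Full Analysis Set (FAS) and Per Protocol (PP).

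- **SAF:** "The SAF includes all included and patients treated by Vent2Cool". The wording is slightly garbled. I read it as patients who were both included and treated, with no evaluation required.
- **FAS:** it "includes all treated patients, who had one post-baseline evaluation". On that reading of the SAF, the FAS is a subset of it.
- **Assignment:** "The main endpoint analysis and secondary endpoint analyses will be based on the Full Analysis Set". No exception is made for safety. The only supportive analysis named is on the PP set, which is narrower still.

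The status of the safety endpoints is clear. Under the trial objectives: "As secondary objectives, the study will aim at demonstrating: the safety of the procedure". Under the primary and secondary endpoints: "Secondary endpoints are shown in Table 1, Table 2", and Table 1 carries the caption "Summary of the secondary safety endpoints".

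The SAF appears in the opening list of sets, and the article promises a disposition table and flow chart for each population. No sentence assigns it an endpoint.

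**The concern.** A safety population exists so that every exposed patient counts in the harm rates, whatever was or was not measured afterwards. The article defines such a set and then bases the harm endpoints on one with an additional entry condition.

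That condition need not be neutral. A treated patient without a post-baseline evaluation is most likely one whose procedure was stopped very early, and the article allows the investigator to stop at any time for safety. Early termination before target temperature is itself a Table 1 endpoint. Hypotension and arrhythmia, also in Table 1, can occur within the first minutes. An exclusion that may depend on the outcome being counted is undesirable in a first-in-human study of about 24 patients, where one event can separate a rate of zero from a rate above zero.

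This is not a detail left to an unseen analysis plan. The article makes the assignment itself, and an analysis plan that put safety on the SAF would contradict it.

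**Working it through.** **Step 1. Reading the assignment.** Table 1 endpoints are secondary endpoints, and secondary endpoints are analysed on the FAS. Table 1 endpoints are therefore analysed on the FAS. The only patients this removes are those in the SAF but not in the FAS, that is, treated patients without a post-baseline evaluation.

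**Step 2. How many patients could that be?** The article does not define a post-baseline evaluation, so I set the measurement schedule against two readings.

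| Reading | First qualifying observation | SAF minus FAS |
|---|---|---|
| Any reading after the start | Core temperature, every minute from the start (Table 2) | None, or close to none |
| A scheduled blood gas or haemodynamic assessment | 10 min after the start (Table 1) | A patient stopped before 10 min with no later qualifying assessment |

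Even on the second reading, a patient stopped early and still followed has assessments from 1 h after the procedure (Table 1) and vital status at Day 28 (Table 2). To fall outside the FAS, the patient must have none of these, or none that is accepted as an evaluation.

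**Step 3. Which endpoints could be affected?** Early termination is the clearest case, because the fact of stopping can be recorded without any measurement. Hypotension and arrhythmia are possible if a monitor observation is not treated as an evaluation. Severe desaturation is a poor example: it must last at least 5 minutes during the procedure, so a patient stopped at once cannot meet the definition.

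**Step 4. The plan's own figure.** The article uses the Wilson score interval. With p = x/n and z = 1.96:

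- centre = (p + z²/2n) / (1 + z²/n)
- half-width = z × √(p(1−p)/n + z²/4n²) / (1 + z²/n)

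For 19/24, z²/n = 3.8415/24 = 0.1601.

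- centre = (0.7917 + 0.0800)/1.1601 = 0.7514
- half-width = 1.96 × √(0.006872 + 0.001667)/1.1601 = 0.1561
- interval = 59.5% to 90.8%, as stated in the article

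**Step 5. Illustration with the same method.** The number of treated patients without an evaluation is not given. I assume 0, 1 or 2, that each had the event in question, and that no event occurred among the others. For x = 0 the upper limit reduces to z²/(n + z²); for example, 3.8415/26.8415 = 14.3% when n = 23.

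| Treated | Excluded from FAS | SAF rate (95% CI) | FAS rate (95% CI) |
|---|---|---|---|
| 24 | 0 | 0/24 = 0% (0 to 13.8%) | 0/24 = 0% (0 to 13.8%) |
| 24 | 1 | 1/24 = 4.2% (0.7 to 20.2%) | 0/23 = 0% (0 to 14.3%) |
| 24 | 2 | 2/24 = 8.3% (2.3 to 25.8%) | 0/22 = 0% (0 to 14.9%) |

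The planned number is 24 analysable patients, so more may be treated. With 25 treated and one excluded, the rates are 1/25 = 4.0% (0.7 to 19.5%) and 0/24 = 0% (0 to 13.8%). With two other events among 24 treated and one patient excluded, they are 3/24 = 12.5% (4.3 to 31.0%) and 2/23 = 8.7% (2.4 to 26.8%).

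If the one excluded patient had no event and nobody else did, the comparison is 0/24 (upper limit 13.8%) against 0/23 (upper limit 14.3%). The FAS then looks marginally worse.

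**The case against.** The strongest reply is that the harmful scenario nearly defeats itself. To enter a numerator, an event must be observed after the start, and that observation is, on an ordinary reading, a post-baseline evaluation. A pressure below the hypotension limit is a measurement, and an arrhythmia is seen on an ECG. Temperature is read every minute. A patient who dies on the device still has a vital status and a cause of death. Data collected before a withdrawal are kept. This largely stands, and it is why the expected effect is small. It does not fully dispose of early termination, which can be recorded without a measurement, and it depends on a definition that the article does not give.

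A second reply is that naming a Safety population signals that it will be used, and that a condensed article leaves the assignment of tables to sets to the full protocol or analysis plan. The first half is fair, and the sentence may be a drafting slip. The second would hold if the article were silent, but it assigns secondary endpoints to the FAS without exception.

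Two stronger readings are tempting. A reader might infer that a patient who collapses on the device will vanish from the safety results. The schedule does not support that, since such a patient will almost always have some post-baseline record. A reader might also infer that the article gives two conflicting populations for the same safety endpoints. It does not: no sentence places Table 1 on the SAF. What the text shows is a defined set left without an endpoint, and a general rule without the usual exception for safety.

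**Conclusion.** The point holds as a minor one. As written, the harm endpoints are analysed on a set that can exclude exposed patients, and the Safety population has no endpoint of its own. The likely numerical effect is nil or very small, because the two sets nearly coincide if any reading during the procedure counts as an evaluation.

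If the term is read narrowly, each excluded patient with an event lowers a safety rate by about 4 percentage points at this sample size, as 1/24 against 0/23 shows. That figure rests on three assumptions that the article neither confirms nor excludes: 24 treated patients, at least one without a qualifying evaluation, and an event in that patient. It is an illustration, not a forecast. The primary endpoint and the sample size calculation are outside this point.

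**What to change.** Replace the general assignment with one that separates safety, for example: all Table 1 safety endpoints and all adverse events will be analysed on the SAF, defined as every patient in whom the Vent2Cool patient connector valve was opened; the primary endpoint and the other secondary endpoints will be analysed on the FAS.

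Valve opening is already the article's definition of the start of the procedure, so the SAF would rest on an existing, recordable event. The safety denominator would then no longer depend on what a post-baseline evaluation means.

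The cost is one sentence. It needs no new data and leaves the sample size unchanged. The one downside for the sponsor is that a safety rate may become slightly less favourable.

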**Secondary endpoint of the demonstration of cooling performance**
• Body core (bladder recommended) temperature at start of Vent2Cool procedure and every 1 min for 60 min thereafter. Then, every 15 min for an additional hour and every 2 h until 36 h after the end of Vent2Cool procedure.
• Cooling Rate in body core temperature, calculated as follows: temperature at start of Vent2Cool procedure – 33.5 °C / duration to achieve a core temperature of 33.5 °C
• Delay between the start of the Vent2Cool procedure and body core temperature of 33.5 °C
• Actual duration of the Vent2Cool procedure (from the start of the procedure on the patient to the end of the procedure)
• Delay between ROSC and body core temperature of 33.5 °C.
• Vent2Cool performance parameters based on device data recorded during the Vent2Cool procedure

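### The trigger for the supportive per-protocol analysis is worded against the wrong set: read literally it would almost never fire, and its two readings give opposite instructions for the same data

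*Protocol article*

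**What the plan says.** All the relevant rules stand in one section of the Protocol article, Sample size and statistical analysis.

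- **FAS:** it "includes all treated patients, who had one post-baseline evaluation".
- **PP:** "The PP population includes all patients of the FAS except those with any major protocol deviation". The deviations meant are those that could materially affect the study data.
- **Primary set:** "The main endpoint analysis and secondary endpoint analyses will be based on the Full Analysis Set".
- **Condition for the PP analysis:** "A supportive analysis will be based on the Per Protocol population if more than 10% of patients are excluded from FAS". No denominator is given for the 10%.

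The same section plans for 24 analyzable patients and an expected 19 successes, with a Wilson 95% interval. Table 2, under cooling performance, has body core temperature recorded at the "temperature at start of Vent2Cool procedure and every 1 min for 60 min thereafter".

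**The concern.** The section describes two different exclusions. A treated patient stays out of the FAS for lack of a post-baseline evaluation. A FAS patient stays out of PP because of a major deviation. The analysis being triggered concerns the second exclusion, but the trigger names the first.

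This raises two problems. Followed to the letter, the rule looks at a count that should be close to zero and ignores the deviations that PP exists to remove. If it did fire, PP could not help, because it is a subset of the FAS and lacks the same patients. Followed by its probable intent, the rule gives a different answer for the same data. The trial is open-label and the primary outcome is settled within an hour of starting the device, so the choice between readings could be made with the results in view.

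At stake is the only alternative analysis set that the article names for the primary success proportion.

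**Working it through.** **Inputs.** From the statistical section: 24 analyzable patients, 19 expected successes, a threshold of more than 10%, and the FAS and PP definitions. From Table 2: temperature every minute for 60 minutes. The article gives neither a deviation rate nor a rate of missing evaluations, so those used below are assumptions, shown over a range.

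**1. The plan's own interval.** Wilson limits are [p + z²/(2n) ± z·√(p(1−p)/n + z²/(4n²))] / (1 + z²/n). With p = 19/24, n = 24 and z = 1.96, the centre is 0.751 and the half-width 0.156. This gives 79.2% (59.5% to 90.8%), as the article states.

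**2. Where the 10% cut falls.** 2/24 = 8.3% does not fire and 3/24 = 12.5% does. If the 24 are those in the FAS and the excluded patients come on top, 2/26 = 7.7% does not fire and 3/27 = 11.1% does. The cut is three patients either way.

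**3. Literal reading (treated patients left out of the FAS).** With a temperature reading due one minute after the start, nearly every treated patient has a post-baseline evaluation. The chance of reaching the cut is P(X ≥ 3) = 1 − Σ(k = 0 to 2) C(24,k) q^k (1−q)^(24−k). At an assumed q of 1% it is 0.002, and at 2% it is 0.012. The number of deviators does not enter.

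**4. Probable intent (FAS patients removed to form PP).** The same formula now applies to the rate of major deviations.

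| Assumed deviation rate | Chance that PP runs |
|---|---|
| 5% | 0.12 |
| 10% | 0.44 |
| 15% | 0.72 |
| 20% | 0.89 |

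**5. The readings side by side.** Take 5 deviators and nobody missing from the FAS. Literal count: 0/24 = 0%, no PP analysis. Intended count: 5/24 = 20.8%, PP analysis runs.

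**6. What PP could show, starting from 19/24 = 79.2%.**

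| Removed | All successes | All failures |
|---|---|---|
| 1 | 18/23 = 78.3% (58.1 to 90.3) | 19/23 = 82.6% (62.9 to 93.0) |
| 2 | 17/22 = 77.3% (56.6 to 89.9) | 19/22 = 86.4% (66.7 to 95.3) |
| 3 | 16/21 = 76.2% (54.9 to 89.4) | 19/21 = 90.5% (71.1 to 97.3) |

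With two exclusions, which do not fire the trigger on either reading, the shift from 79.2% is at most +7.2 points (86.4 − 79.2) or −1.9 points (77.3 − 79.2).

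**The case against.** The strongest reply is that the sentence follows closely on the definition of PP as the FAS less major deviators, so exclusion from the FAS most naturally means removal from it to form PP. On that reading the count is exactly the deviation count. A reading that leaves the sentence without purpose is itself evidence that it was not meant. This stands as an account of intent. It does not make the wording right, because the article defines exclusion from the FAS by another criterion and someone applying the text would be entitled to use it.

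It is also said that running PP only when it differs from the FAS by a set fraction is a common rule. That stands too: the 10% threshold is not in itself an error, and on the intended reading PP is skipped only at 0 to 2 exclusions, where it can differ least. Running PP after any exclusion is a simplification suited to 24 patients, not the correction of a mistake.

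Third, the counting rule may be settled in the analysis plan or full protocol, neither of which is shown. For the missing denominator that is fair, and its absence is not held against the article. But the article does state the trigger, and states it against the wrong set.

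Finally, the section promises a summary table and flow chart for each population, so the PP count should be visible whichever reading is used. The PP success rate need not be.

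**Conclusion.** The trigger is miswritten and should be corrected, but the consequence is modest. Taken literally, the supportive PP analysis would almost never run. Taken as probably intended, it runs at 3 or more of 24. One data set can therefore give opposite instructions.

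A reader might infer more: that the trigger is certainly unrelated to deviations, or that the PP analysis will not happen. The documents do not support that, since the intended reading is natural and makes the trigger the deviation count. A reader might also take the distance between 77.3% and 86.4%, about 9 points, as the possible error. That compares two opposite extremes. The shift from 79.2% is at most +7.2 or −1.9 points, and both values lie inside the stated interval of 59.5% to 90.8%.

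The FAS remains primary, PP is described only as supportive, and the trial is a non-comparative pilot sized for precision. No sample size or primary interval changes.

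The conclusion that the literal trigger hardly ever fires assumes that the 10% is taken over treated patients and that temperature is recorded as planned. If the denominator were all included patients, those never started on the device would count as well, which is still not a count of deviations. The firing probabilities rest on assumed rates, and the PP rates on 19 successes in 24.

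**What to change.** Restate the trigger against the PP set: *the supportive analysis will be run if more than 10% of FAS patients are excluded from the PP population*.

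A simpler choice at this sample size is to drop the threshold: *the primary endpoint will also be reported in the PP population whenever at least one FAS patient is excluded from it; the FAS remains primary*.

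Either wording removes the double reading. The change should be made before the data are analysed, and the analysis plan should carry the same wording. The cost is one sentence and, under the second option, at most one extra supportive table. No patients, visits or procedures are added.
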